### Recruitment

#### LGAs

Eligible LGAs: All eligible LGAs will be sent an Information Package including an invitation letter from the DEECD, an outline of the project and an ‘Expression of Interest’ form. Interested LGAs who sign the Expression of Interest will be briefed by the research team and asked about breastfeeding initiatives already underway.

LGAs who meet the inclusion/exclusion criteria and who agree to participate will sign a written agreement. Prior to randomisation, participating LGAs will be grouped according to size (large, medium and small) depending on numbers of births. LGAs will be allocated to the large category if they have more than 2,500 births per year, to the medium if they have between 1,000 and 2,500 births per year, and to the small category if they have fewer than 1,000 births per year. Randomisation will be stratified by these size categories. If there are more LGAs interested in participating than are required, then excess LGAs will be included in the comparison group. For example if there are four large LGAs with relatively similar numbers of births (and there are more LGAs than required) then two of these LGAs will be included in the comparison group. This process will be made explicit to LGAs in the briefings with the research team.

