#### Primary outcome

In relation to the trial hypotheses, each intervention group will be compared to the standard care group using intention to treat analysis. For the primary outcome, proportions of women giving their baby *any* breast milk at four months will be compared using odds ratios derived using logistic regression. A multivariate analysis will be carried out to adjust for known potential confounders, as well as for the baseline breastfeeding rates of each LGA. In all analyses, adjustment will be made for clustering at the MCH centre level, and the LGA strata (i.e. LGA size) will be taken into account. Results will be presented as adjusted odds ratios, with 95% confidence intervals.

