#### Secondary outcomes

All comparisons that involve percentages of breastfeeding will be undertaken using the same method as the primary outcome, with each intervention group compared to the standard care group using intention to treat analysis. Comparison of means will be undertaken for continuous variables such as breastfeeding duration using t-tests where data were normally distributed or medians compared otherwise using Mann-Whitney U tests.

Data obtained from women’s surveys will be explored using descriptive statistics. Analysis for pre-coded responses will be undertaken using descriptive statistics, and frequencies and percentages presented. Outcomes will be presented by trial arm; with statistical comparisons undertaken when appropriate using the chi-square test. Women’s responses to open-ended questions will be analysed inductively and grouped into analytical descriptive categories [46]. The categories will be discussed by the research team and final themes agreed. Comparisons will be made between trial arms where possible.

Data from the focus groups with SILC-MCHNs and face-to-face interviews with MCH co-ordinators or managers will be transcribed and grouped into analytical descriptive categories using basic thematic analysis [46]. SILC-MCHN survey data will be analysed using a mix of quantitative (for pre-coded responses) and qualitative (for open-ended responses) methods.

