### Trial status

Twenty one Victorian LGAs were eligible to participate in SILC. Eighteen of these LGAs submitted a written Expression of Interest to participate. Following briefing sessions with these 18 LGAs, four were deemed ineligible to participate as they had ongoing initiatives in place similar to one or both of the interventions. A further four declined to participate. The remaining ten LGAs, comprising three large, three medium and four small LGAs, agreed to participate and be randomised. During randomisation, one LGA from each group (small, medium, large) was randomly assigned to be the comparison LGA for that group, one was assigned to receive home-visits by a SILC-MCHN, and one assigned to received home-visits and drop-in centre access. Because there were four LGAs in the small group, two LGAs were randomly assigned to be comparison LGAs.

The interventions commenced in LGAs in July 2012 and ran for a nine month period until March 2013. Data collection is now complete. Analysis and final writing up is underway. Final results are expected in 2015.

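### Duration and non-feeding survey items are to be compared with crude tests although small LGAs were allocated 2:1:1 and the other strata 1:1:1, which leaves those comparisons open to confounding by LGA size

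*Protocol article*

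**What the plan says.** **Allocation.** Randomisation was stratified by annual births. The Recruitment section (LGAs) sets the rule for surplus: "If there are more LGAs interested in participating than are required, then excess LGAs will be included in the comparison group". Trial status reports what happened: "The remaining ten LGAs, comprising three large, three medium and four small LGAs, agreed to participate and be randomised". One LGA per stratum went to each arm, with one exception: "Because there were four LGAs in the small group, two LGAs were randomly assigned to be comparison LGAs".

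**Analysis.** The Primary outcome section specifies logistic regression. One sentence there is worded to cover every analysis: it promises to allow for clustering by MCH centre and adds that "the LGA strata (i.e. LGA size) will be taken into account". The Secondary outcomes section sends comparisons of breastfeeding percentages to that same method. For other outcomes it names different tests. On duration: "Comparison of means will be undertaken for continuous variables such as breastfeeding duration using t-tests", with Mann-Whitney U tests where the data are not normal. On pre-coded survey responses: "Outcomes will be presented by trial arm; with statistical comparisons undertaken when appropriate using the chi-square test".

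**The concern.** A small LGA had a 2/4 chance of becoming a comparison LGA; a large or medium LGA had a 1/3 chance. When the allocation ratio differs between strata, ignoring the strata costs more than precision: stratum and arm become associated by design. If an outcome also varies with stratum, the crude arm difference is shifted even when the intervention does nothing.

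The tests named for duration and for the remaining survey items cannot, as named, take size into account. If the general sentence under Primary outcome governs them, the two sections conflict. If that sentence covers only the primary outcome, the imbalance goes uncorrected. Either way the text needs attention.

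A correction for clustering alone would not cure this. It widens the standard error but leaves the estimate and the by-arm percentages where they were. Both intervention arms are compared with the same comparison arm, so a shift would tend to appear in both contrasts and could be read as a consistent effect of home visiting on duration, breastfeeding problems, use of support or views of services.

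**Working it through.** **1. The allocation count reproduces.** 3 + 3 + 4 = 10 LGAs. Comparison: 1 + 1 + 2 = 4. Each intervention arm: 1 + 1 + 1 = 3.

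**2. Inputs.** From the Recruitment section (LGAs) and the inclusion criteria: the large band starts above 2,500 annual births, the medium band runs from 1,000 up to 2,500, the small band lies below 1,000, and the eligibility floor is 450. Assumptions: large LGAs have at most 4,000 births (no ceiling is given); survey response is equal across LGAs; and, for this step, LGAs in the same stratum are equal in size.

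**3. Share of women from small LGAs.** With l, m and s births in a large, medium and small LGA:

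- comparison arm: 2s / (l + m + 2s)
- each intervention arm: s / (l + m + s)

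| l / m / s | Comparison | Intervention | Gap (points) |
|---|---|---|---|
| 2,501 / 1,000 / 999 | 1,998/5,499 = 36.3% | 999/4,500 = 22.2% | 14.1 |
| 3,000 / 1,500 / 700 | 1,400/5,900 = 23.7% | 700/5,200 = 13.5% | 10.3 |
| 4,000 / 2,500 / 451 | 902/7,402 = 12.2% | 451/6,951 = 6.5% | 5.7 |

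**4. Shift with no intervention effect.** The crude difference is the sum over strata of (intervention share − comparison share) × stratum mean. If only small LGAs differ, this equals gap × outcome difference in size. At the middle row (gap 0.103):

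- 5-point outcome difference (assumption): 0.5 points
- 10 points: 1.0 point
- 20 points: 2.1 points
- no difference: 0

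With a 10-point difference, the three rows give 0.6 to 1.4 points. For mean duration the same multiplier applies: each week by which small LGAs differ moves the crude mean difference by about 0.1 week.

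**5. Realised sizes.** Step 3 gives every arm LGAs of the same size, which need not hold. An extreme case within the assumed limits reverses the gap: a comparison arm of 4,000 + 2,500 + 2 × 451 has 12.2% from small LGAs, and an intervention arm of 2,501 + 1,000 + 999 has 22.2%. A simulation with sizes uniform within the bands (large capped at 4,000) gives average shares of 22.6% and 12.7%, and an average shift of 1.0 point in each contrast when small LGAs differ by 10 points. The two contrasts had the same sign in 98% of draws if only small LGAs differ, 93% under a linear gradient with size, 76% if only large LGAs differ and 67% if only medium LGAs differ.

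**6. After adjustment.** If the outcome depends only on stratum, the within-stratum arm difference is 0 in all three strata, so any weighted average of them is 0.

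**7. Scale against clustering.** The protocol's design effect reproduces: 1 + 85 × 0.02 = 2.70. A nominal 5% test that ignores it has true type I error 2 × [1 − Φ(1.96/√2.70)] = 23%. With 30 or 50 women per centre (assumptions) the design effect is 1.58 or 1.98, and the error about 12% or 16%.

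**The case against.** **No bias has been demonstrated.** This stands. The article describes breastfeeding gaps by socioeconomic area and between individual LGAs, not by number of births. A reader might infer from the 2:1:1 split that the comparisons are biased; the documents support only that they are open to bias. What makes an association plausible is indirect: size was chosen as the stratification factor, and planned drop-in hours and nurse hours vary with it.

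**Same direction in both arms.** A reader might also infer that the artefact must point the same way in both contrasts. That is true in expectation only. The realised LGA sizes are not reported, and step 5 shows the gap can reverse. For the same reason, 5.7 to 14.1 points is a range under equal sizes, not a bound.

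**False-positive rates.** It is tempting to say that size imbalance alone lifts the error rate from 5% to some higher figure. These tests do not start at 5%: at the protocol's own ICC they are already well above it because they ignore clustering, which is probably the larger fault.

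**Reach.** Every stated hypothesis concerns the proportion receiving any breast milk at three, four or six months, and all of these use the adjusted logistic model. The survey items are mainly descriptive, with chi-square tests only where judged appropriate. This stands and limits the consequence.

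**The general sentence already covers it.** Partly. It is worded for all analyses but sits under the Primary outcome heading, and the tests then named cannot deliver it. The conflict remains until one section is changed.

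**Conclusion.** The point holds in a limited form. The unequal allocation in the small stratum is documented, the named tests ignore it, and they do not meet the protocol's own statement about strata and clustering. The affected outcomes are breastfeeding duration and pre-coded survey items other than breastfeeding percentages; the primary and secondary hypotheses are untouched.

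The size is modest: an expected shift of about 0.5 to 2 points if small LGAs differ from the others by 5 to 20 points, and zero if they do not differ. That rests on assumed LGA sizes and outcome differences and on equal survey response. It is worth correcting because the correction is cheap and the strata were already used to randomise, not because a trial conclusion has been shown to depend on it.

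**What to change.** In the Secondary outcomes section, replace the t-test, Mann-Whitney and chi-square comparisons with regression models that include arm and LGA-size stratum and allow for clustering, as the Primary outcome section already promises: linear or another suitable model for duration, logistic or multinomial for pre-coded survey items. Report raw by-arm percentages as descriptive only, next to the stratum-adjusted estimates.

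Reweighting is not needed. Giving the two small comparison LGAs half weight, for instance, would not produce a common stratum mix, because large and medium LGAs can also differ in size between arms. Baseline tables need no restandardising.

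The cost is a revised sentence or two and minor extra programming. No new data are needed, and Trial status says the analysis was still under way.

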### Timelines

The project, from design of the interventions to data collection and analysis is expected to take three years. Figure 2 shows the timeline estimates.

**Figure 2 Fig2:**
[figure not shown]
**Timeline estimates for the SILC trial.** The figure gives timeline estimates for the intervention running for a nine month period in SILC LGAs. The first two months will be a run-in period. Data collected during the run-in period will not be used in the final analysis.

### Ethical considerations

#### Consent

LGAs will sign a written agreement to participate and be randomised. For the postal survey, women will be provided with information about the study in a covering letter mailed to them with the survey, and consent will be implied by the completion and return of the questionnaire.

#### Ethics approvals

Approval for the study has been granted by:

La Trobe University Human Ethics Committee (project number 11–068);The Department of Education and Early Childhood Development (project number 2011_001305).

#### Risks/inconveniences/benefits

It is not anticipated that this trial poses any risks to LGAs or to women who participate. It is possible that women will benefit from the interventions, but this is unknown. While some women with breastfeeding difficulties may experience stress associated with their breastfeeding problems, MCHNs in both intervention and comparison areas have both the skill set necessary and the knowledge of available support services in order to address these issues.

The postal survey sent to women will contain contact details of support services available to them. The contact details of the research team and the La Trobe Ethics Committee will also be provided. Every effort will be made to ensure that women who should not receive a survey (as per the exclusion criteria) are not sent one.

### Dissemination

At trial completion, a final report will be submitted to the DEECD. All LGAs will be de-identified in this report, a summary of which will be available on their website. All participating LGAs will receive a separate report of outcomes for women in their municipality, including postal survey responses. SILC presentations will also be undertaken in each LGA following trial completion, and at both national and international conferences.

### Project governance

#### Meetings

It is anticipated that the research team will meet fortnightly throughout the project, and more often as necessary. The research team will also meet regularly with the DEECD.

#### Study advisory group

An advisory group will be established to bring together a group of people with relevant expertise and interest in the trial. The group will contribute ideas and advice to the research team through all stages of the project, comment on drafts of materials and resources developed to support the project (e.g. questionnaires, reports), participate in discussion of the findings and their implications for future research and implementation strategies and assist in developing appropriate strategies for disseminating the findings of the project. Terms of Reference have been developed (see Additional file 1). Overall responsibility for the conduct of the research, analysis of the data and publication of the findings remains with the research team.

### Trial status

Twenty one Victorian LGAs were eligible to participate in SILC. Eighteen of these LGAs submitted a written Expression of Interest to participate. Following briefing sessions with these 18 LGAs, four were deemed ineligible to participate as they had ongoing initiatives in place similar to one or both of the interventions. A further four declined to participate. The remaining ten LGAs, comprising three large, three medium and four small LGAs, agreed to participate and be randomised. During randomisation, one LGA from each group (small, medium, large) was randomly assigned to be the comparison LGA for that group, one was assigned to receive home-visits by a SILC-MCHN, and one assigned to received home-visits and drop-in centre access. Because there were four LGAs in the small group, two LGAs were randomly assigned to be comparison LGAs.

The interventions commenced in LGAs in July 2012 and ran for a nine month period until March 2013. Data collection is now complete. Analysis and final writing up is underway. Final results are expected in 2015.

## Discussion

Breastfeeding initiation is high in Australia, but many women stop in the early months postpartum, especially those in lower socioeconomic communities. We have designed this trial to address this by situating the study in areas with low breastfeeding rates and testing two strategies with the potential to provide support for women in the community to maintain breastfeeding. If shown to be effective, the intervention programs have been pragmatically designed so that if either increased the maintenance of breastfeeding, then incorporation into practice across the state should be readily achievable.

## Abbreviations

ABA: Australian Breastfeeding association
DEECD: Department of Education and Early Childhood Development
EBM: Expressed breast milk
KAS: Key Ages and Stages
LGA: Local Government Area
MAV: Municipal Association of Victoria
MCH: Maternal and Child Health
MCHN: Maternal and Child Health Nurse
SILC: Supporting breastfeeding In Local Communities
SILC-MCHN: SILC Maternal and Child Health Nurse.
